### Outcomes

The primary outcome is that the views of GPs, MPAs, and patients be obtained, on the supply and utilization of health services during the COVID-19 pandemic, addressing positive as well as negative aspects, such as:

aspects of underutilization/undersupply;possible identification of services that turned out not to be necessary;unanticipated benefits like improvement of organizational matters and use of virtually-delivered care.

Piloting the structural development of the network, secondary outcomes are the number of participating GPs and MPAs and the number of participating patients. The number of participating GPs will be compared in terms of whether or not they are members of RESPoNsE.

### Data analysis

Data from the returned self-reported questionnaires will be entered manually into a Microsoft Excel spreadsheet and imported into IBM SPSS software (V.28) for data cleaning and analyses. Descriptive statistics (such as frequencies and proportions), summary statistics (such as means with standard deviations or median with interquartile range, as appropriate), and the number of missing values for each variable will be reported. Missing values will not be imputed.

The association of selected demographic and professional characteristics regarding respondents´ views and experiences will be verified with the chi-square test of independence for categorical variables and parametric or non-parametric tests for continuous variables, depending on the distribution. A comparison of GPs´and MPAs´ answers will be performed accordingly. The threshold for significance will be set at 0.05. Multivariate regression analyses will be applied to selected items where appropriate.

Qualitative data from the interviews and focus groups will be analyzed using thematic analyses based on a combined inductive and deductive approach [68]. Data analysis and coding will be facilitated by using the software MAXQDA 2022, release 22.1.1. One author of the multidisciplinary research team will start categorizing and coding the first interviews and develop a coding framework, which then will be discussed with the other members of the research team before being applied to the proceeding interviews.

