### Study design and setting

The study will be carried out in three German federal states that are covered by the RESPoNsE network (Berlin, Brandenburg, and Thuringia), comprising approximately eight million inhabitants.

Due to the explorative nature of the study, no sample size calculation was undertaken. Every GP in Berlin and Brandenburg who is statutory health insurance registered (approximately n = 4.100) may take part in the study. The response rate will be a secondary outcome, comparing the rates for GPs who already are part of the RESPoNsE network with those who are not. As other surveys in the Thuringia GP practices are taking place at the same time, only those practices that already are members of RESPoNsE (n = 70) are invited to take part in the study. There are no exclusion criteria.

The GPs have received a postal invitation to take part in the study. MPAs may take part in the study independently of the GPs in the same practice but, as we only have information on the GPs working per practice (and not the MPAs), MPAs will only receive information about the study from the GP who received the letter at their practice.

In line with previous work and similar surveys with GPs, we expect a response rate of about 25% [56, 57]. We expect the response rate to be higher among GPs who are already a part of the RESPoNsE network. As we don`t know how many MPAs are working in the practices we will not be able to calculate a response rate for the MPAs.

The letter to the GPs consists of:

a study information;the questionnaire for GPs (to be filled out anonymously);the questionnaire for MPAs (to be handed out to interested MPAs in the same practice and filled out anonymously by as many MPAs as are willing to take part in the study—the questionnaire be copied if necessary);a prepaid return envelope;a response form (S1 Form), asking for their readiness to take part in the survey or in the further portions of the study (to be filled out with contact details and to be sent back separately via fax or mail);The GPs and MPAs in Berlin and Brandenburg who are not yet members of the RESPoNsE network are also provided with information on network activities and aims and will be asked to express their interest to be part of the network.

After 4 weeks the same letter was sent as a reminder to those GPs who had not yet returned their response form (Fig 1).

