	Requirements/resources in order to maintain health care provision during the pandemic (for example, material, qualification, information).	strongly agree–agree—neutral- disagree -strongly disagree
	*Example statement*: *“In order to maintain the provision of care under pandemic condition we need … better qualified personnel”*	
GPs only	Subjective assessment of usefulness of information by different professional associations and organizations during the pandemic (for example, the General Medical Council, Standing Committee on Vaccination, Federal Centre for Health Education, German College of General Practitioners and Family Physicians).	Very helpful–rather helpful–neutral–rather not helpful–not helpful at all –don´t know
	*Example statement*: *“How would you assess the information given during the pandemic by the… German College of General Practitioners and Family Physicians“*	
MPAs only	Personal anxieties and concerns during the pandemic (for example, stress, risk of infection and health issues, social conflicts, economical burdens).	strongly agree–agree -neutral- disagree -strongly disagree
	*Example statement*: *“What are the primary issues of fears and worries for you during the pandemic… constant stress “*	

Participating GPs and MPAs will be asked to fill in a second questionnaire after 12 to 18 months. In this way, we will explore which views and possible changes in health services persist over time. As the questionnaires will be anonymous, the comparison will be made on an aggregated level.

The GPs who participated in the first survey will also be asked to cooperate in the patient survey. Those who indicate an interest on the response form will be contacted again with further information on the proceedings and will be asked to consent into participating in the study. From a previous study (not yet published), we expect about 50 to 100 GPs to take part in this portion of the study. Participating GPs may indicate whether they expect to successfully distribute questionnaires for 50 or 100 patients during the standardized study period of four weeks. Questionnaires will be sent to the practices accordingly to be distributed among patients who sit in the waiting room. Patients will be provided with information on the study, asked to fill in the questionnaire anonymously, and to place it in a pre-prepared box. After the given study period, the practice team will send back the questionnaires using a prepaid envelope.

Inclusion criteria are:

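### The patient survey samples patients in clusters by practice, but the only test named for categorical answers assumes independent respondents, so p-values for practice-level factors would be too small

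*Protocol article*

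**What the plan says.** **Sampling of patients.** Under the heading Quantitatively: Surveys, the article expects about 50 to 100 GPs to join the patient survey. On volume it says: "Participating GPs may indicate whether they expect to successfully distribute questionnaires for 50 or 100 patients during the standardized study period of four weeks". Forms are given to patients in the waiting room and collected in a box. On return it says: "After the given study period, the practice team will send back the questionnaires using a prepaid envelope".

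**Sampling of MPAs.** Under Study design and setting, MPAs are reached only through the GP who received the letter, and their questionnaire is to be "filled out anonymously by as many MPAs as are willing to take part in the study". The number of MPAs per practice is unknown to the investigators.

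**Analysis.** Data analysis has one description for the returned questionnaires. Associations between selected demographic and professional characteristics and respondents' views "will be verified with the chi-square test of independence for categorical variables", with parametric or non-parametric tests for continuous variables. It adds: "A comparison of GPs´and MPAs´ answers will be performed accordingly". It also states: "The threshold for significance will be set at 0.05". Regression is left open: "Multivariate regression analyses will be applied to selected items where appropriate".

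The article does not mention clustering by practice, an ICC, a multilevel or GEE model, or a robust variance. It plans frequencies, proportions, means with SD and medians with IQR, but no confidence intervals.

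**The concern.** A chi-square test of independence treats each respondent as a separate piece of information. Here the patients come in batches from the same waiting rooms. Many of the study's themes (appointments, telephone and video care, practice organisation) are decided by the practice. Box 1 itself says that GPs largely settle staffing, hours and organisation on their own. Two patients of one practice will therefore tend to answer more alike than two patients of different practices.

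The consequence depends on the factor tested. If the factor is the same for everyone in a practice, the real sample size for that comparison is closer to the number of practices than to the number of patients, and the plain test rejects too often. An apparent difference between regions, or between town and country, could then be reported as significant when it reflects only variation between individual practices. The article plans to publish the results and present them to political and professional decision-makers.

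**Working it through.** The article gives no sample size, ICC or design effect, so there is no planned figure to reproduce.

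**Inputs from the article.** 50 to 100 GPs; 50 or 100 forms distributed by each; threshold 0.05. Forms distributed: 50 × 50 = 2,500 up to 100 × 100 = 10,000.

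**Assumptions, not in the article.** ICC of patient answers 0.02 to 0.05 (wider range 0.01 to 0.10). Forms returned per practice, m: 25, 50 or 100; the values 50 and 100 would need every distributed form to come back. One participating GP is counted as one practice.

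**Formulas.**
- Design effect: DE = 1 + (m − 1) × ICC.
- True size of a nominal 5% test of a two-level factor that is constant within practice: 2 × [1 − Φ(1.96 / √DE)].
- The unadjusted standard error of a patient proportion is too small by a factor of √DE.

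| m | ICC | DE | √DE | True size |
|---|---|---|---|---|
| 25 | 0.02 | 1 + 24 × 0.02 = 1.48 | 1.22 | 0.107 |
| 25 | 0.05 | 1 + 24 × 0.05 = 2.20 | 1.48 | 0.186 |
| 50 | 0.02 | 1 + 49 × 0.02 = 1.98 | 1.41 | 0.164 |
| 50 | 0.05 | 1 + 49 × 0.05 = 3.45 | 1.86 | 0.291 |
| 100 | 0.02 | 1 + 99 × 0.02 = 2.98 | 1.73 | 0.256 |
| 100 | 0.05 | 1 + 99 × 0.05 = 5.95 | 2.44 | 0.422 |

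At the low end (50 practices × 50 forms), 2,500 respondents carry the information of 2,500 / 1.98 ≈ 1,263 independent ones at ICC 0.02, or 2,500 / 3.45 ≈ 725 at ICC 0.05. At the high end, 10,000 shrink to 10,000 / 2.98 ≈ 3,356 or 10,000 / 5.95 ≈ 1,681.

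**Simulation check, patients** (75 practices, beta-binomial answers with mean 0.5, ICC 0.01 to 0.10, ordinary 2 × 2 test):
- Factor constant within practice: size 0.09 to 0.27 at m = 25, 0.11 to 0.42 at m = 50, 0.16 to 0.55 at m = 100. At ICC 0.05 the values are 0.19, 0.28 and 0.42, in line with the table.
- Factor partly clustered (its own ICC 0.05 or 0.10): about 0.05 to 0.08, 0.05 to 0.11 and 0.06 to 0.17 for the same three values of m.
- Factor varying only within practices: 0.04 to 0.06, so essentially no inflation.

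**Simulation check, staff** (500 practices, ICC 0.05 to 0.20; numbers per practice assumed):
- MPAs at 2 to 5 per practice: 0.06 to 0.14 for a practice-level factor, 0.04 to 0.05 for a factor varying only within practices.
- GPs against MPAs of the same practices (one GP, 1 to 3 MPAs): 0.03 to 0.05, nominal to conservative, because the shared practice effect cancels in the difference.

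**The case against.** **The study is exploratory.** There is no sample size calculation, the abstract calls the questionnaire analysis descriptive, and the primary outcome is to obtain views. This stands. No confirmatory conclusion rests on these p-values, and clustering does not by itself bias the reported percentages. It lowers the weight of the point but does not make the named test fit the sampling.

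**The patient tests are inferred.** The listed characteristics, including practice location, belong to the GP and MPA questionnaire; the patient questionnaire is not shown, and no test of patient answers by region is spelled out. This stands in part. The analysis sentence covers respondents to the returned questionnaires without limiting it to staff, so the plain reading includes patients. The size of the harm is still conditional on a practice-level or strongly clustered factor being tested.

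**The article is condensed.** A practice code is an operational detail that an article may omit, and the open regression sentence leaves room for a multilevel model. This also stands: the absence of a code is not a fault in itself. The test, however, is named, and as named it assumes independence.

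**Stronger readings to avoid.** A reader might infer that all p-values in the study are far too optimistic. The documents do not support that: age or gender mixed evenly within practices is barely affected, and the limit of 100 per practice applies only to patient forms distributed. A reader might also infer that planned confidence intervals are too narrow, but none are planned. Nor does the sharing of practices by GPs and MPAs make their comparison optimistic; it errs, if anything, the other way.

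**Conclusion.** The concern holds for the patient survey, and there for factors that are fixed by the practice or strongly clustered. For such factors, a nominal 5% chi-square test has a true size of roughly 11% to 42% across 25 to 100 returned forms per practice and an assumed ICC of 0.02 to 0.05. Unadjusted standard errors of patient proportions, if they are ever reported, would be too small by a factor of about 1.2 to 2.4 under the same assumptions. For MPAs the inflation is modest, about 6% to 14% for practice-level factors, and rests on assumed cluster sizes. All these figures depend on ICCs that the article does not give. Severity is moderate: the tests are exploratory, but the mismatch is in the method as written and is easily avoided.

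**What to change.** **Patient survey.** According to Study status, this survey was still to be prepared and conducted. Before it starts, print a random practice code on each patient form, or mark each batch with one when it comes back. Because forms already return by practice, this does not identify any patient. Without a code, forms from different practices cannot be separated once mixed.

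**Analysis wording.** For patient data, replace the plain chi-square test with a Rao-Scott corrected test, or with GEE or mixed models (ordinal for the Likert-type items, if used) with practice as the cluster. Report the ICC for the main items. If standard errors or intervals for patient proportions are added, make them cluster-robust.

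**MPA survey.** The first round began in March 2022 as an anonymous survey. A common envelope number could be used in the 2023 repeat, but only if data-protection rules allow: many practices are single-handed, and a link combined with age, gender and location could narrow down individuals. Otherwise, state the unmodelled clustering as a limitation.

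**Cost.** One code, one extra data column, a change of analysis wording, and less favourable p-values for practice-level factors.

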### Dissemination of results

Results will be published in peer-reviewed open-access journals.

A symposium will be held, presenting and discussing the results with GPs, MPAs, members of the public, and representatives of political and professional decision-makers.

## Discussion

This project addresses the key role GPs and MPAs have in the care of patients during the pandemic, with or without COVID-19. They are usually the first point of contact and it is them who will be “left to manage the aftermath” [2], confirming their “first in, last out” role [3, 69].

The study will give GPs, MPAs, and patients the opportunity to voice their concerns, struggles, and needs during the COVID-19 pandemic. It will explore the impact of changing GP care during the pandemic, including lessons learned, and will help to assess which transformations might prevail [3, 70, 71].

The study will also provide a basis for further overdue discussions on reasonable appreciation and validation of the role of primary care during the pandemic, of the contribution of MPAs in a functioning GP care service, and support needs and how these can be addressed.

Integrating the patient perspective, the mixed quantitative and qualitative approach may also help to obtain a new view on previously perhaps overused care [72].

### Limitations

The COVID-19 pandemic so far has come in waves with very different demands on GP care. The current pandemic phase, with a dominating Omicron variant, and a seven-day-incidence of about 1,800 new cases per 100,000 inhabitants in Germany at the time of writing the protocol, may well have subsided by the time of data collection. The subjective impression of health care utilization and uptake may reflect the moment rather than the various phases of the pandemic.

The study is to be conducted in three federal states of Germany. Therefore, it might not represent the view of GPs, MPAs, and patients in other regions of Germany. On the other hand, the three regions compromise heterogenous economic and social conditions from metropolitan to rural areas.

A frequent problem in survey research on GPs is the low response rate. There is some controversy over the potential of response bias [73–75]. Several feasible strategies to improve the response rate failed to show an effect [56, 76]. We hope that, by keeping the questionnaires relatively short and addressing currently relevant topics, we attain a reasonable response rate.

## Study status

Ethics and data protection approvals have been obtained.

The questionnaire for GPs and MPAs has been constructed and piloted.

Data collection from the questionnaire for GPS and MPAs began in March 2022.

The patient focus groups were conducted in April 2022.

Interviews and the patient survey will be prepared and conducted over the next six months.

In 2023, the GP and MPA survey will be repeated.

## Ethical considerations

Ethical approval was obtained from the Ethic Commission of Charité–Universitaetsmedizin Berlin, Germany (EA2/303/21, January 20, 2022) and from Universitätsklinikum Jena, Thuringia (2022-2537-Bef, January 31, 2022).

## Data availability statement

The study will generate two kinds of data: the quantitative data of the surveys will be collected and analyzed anonymously. All variables will be reported descriptively with adequate summary measures. Original data will be available upon reasonable request. The qualitative data of the transcribed interviews´ data are more sensitive: before taking part, patients will give their written consent that these data may be used for the purpose of this study only. This data will not be shared beyond the research team.
